Additional analyses treating survival and PFS as time to event endpoints will be performed i.e.: Kaplan-Meier plots will be produced. Survival will be measured, regardless of any re-induction, from the date of the first ipilimumab dose given on-study until date of death. Survival time for subjects whose date of death is unknown, will be censored at the last date of contact. PFS will be measured, regardless of any re-induction, from the date of the first dose of ipilimumab until the first on-study documented date of progression as per irRC, or date of death, whichever comes first. PFS time of subjects not known to progress or die, will be censored at the date of the last tumor assessment. Median survival, median PFS, survival rate at 1 year and PFS rate at 6 months, all as derived from the Kaplan-Meier curves, will also be presented, together with two-sided 95%CI.

Safety will be reported for 70 days post last treatment. This period will be considered the on-study safety period. The analysis of safety will be based on the frequency of AEs, relationship to ipilimumab and their severity for all treated subjects (i.e.: all subjects receiving at least one dose of ipilimumab). Worst toxicity grades per subject will be tabulated for all AEs. Additionally, drug-related grade 3 or more AEs, immune-related, and serious AEs will be tabulated separately, and listings by subject will be produced for all deaths, all SAEs and all AEs leading to discontinuation of study drug.

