**6.1.1.4. End of Treatment Visit**

The end of treatment visit will be performed 10 weeks after last administration of study therapy. The following procedures will be performed during end of treatment visit:

- Measurements of vital signs (resting systolic and diastolic blood pressure, pulse, respiratory rate, and temperature) and weight
- Physical examination
- ECOG Performance Status
- Clinical laboratory tests
  - Hematology
  - Serum chemistry
  - TSH, Free T4
  - Urinalysis (urine dipstick for protein)
- Assessment of signs and symptoms

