## 6.2. Safety Assessments

All patients who receive at least one dose of ipilimumab will be considered evaluable for safety parameters. Additionally, any occurrence of nonserious or SAE from time of consent forward, up to and including follow-up visits, will be reported. See Section 8: Adverse Event Reporting.

Safety will be evaluated for all treated patients using the National Cancer Institute (NCI) Common Terminology Criteria for Adverse Events (CTCAE), Version 4.0 ([http://www.acrin.org/Portals/0/Administration/Regulatory/CTCAE\\_4.02\\_2009-09-15\\_QuickReference\\_5x7.pdf](http://www.acrin.org/Portals/0/Administration/Regulatory/CTCAE_4.02_2009-09-15_QuickReference_5x7.pdf)). Safety assessments will be based on medical review of adverse event reports and the results of vital sign measurements, physical examinations, and clinical laboratory tests.

Appendix 10 to 15 presents algorithm for safety and provides recommendations for immunerelated adverse events. The algorithm should help to inform and enhance patient care and reduce the risk of immunerelated AEs and to initiate therapy and minimize complications.

Immunerelated AEs are generally manageable using symptomatic or immunosuppressive therapy as recommended through detailed diagnosis and management guidelines as described in the investigators' Brochure (IB version no: 13 dated 26-Aug-2010). The management guidelines for general immune-related AEs and ipilimumab-related gastrointestinal toxicities, hepatotoxicity, endocrinopathy and neuropathy are provided in the IB Appendices 6,7,8,9, and 10 respectively. In addition if necessary please contact the study core center.

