#### 8.2. Assignment of Adverse Event Intensity and Relationship to Investigational Product

The following categories and definitions of causal relationship to investigational product as determined by a physician should be used:

- **Related:** There is a reasonable causal relationship to investigational product administration and the adverse event.
- **Not Related:** There is not a reasonable causal relationship to investigational product administration and the adverse event.

The expression “reasonable causal relationship” is meant to convey in general that there are facts (eg, evidence such as de-challenge/re-challenge) or other arguments to suggest a positive causal relationship.

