#### **8.3.3. Non-serious Adverse Events**

The collection of non-serious AE information should begin from time of consent forward until end of treatment.

If an ongoing nonserious AE worsens in its intensity, or if its relationship to the investigational product changes, a new nonserious AE entry for the event should be completed. Nonserious AEs should be followed to resolution or stabilization, or reported as SAEs if they become serious. Follow-up is also required for nonserious AEs that cause interruption or discontinuation of investigational product, or those that are present at the end of study participation. Subjects with nonserious AEs at study completion should receive post-treatment follow-up as appropriate.

All identified nonserious AEs must be documented and described in the medical record.

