#### 9.3.2. Secondary Efficacy Parameters

To assess safety and additional efficacy parameters of the ipilimumab treatment.

Secondary endpoints are

- Safety / toxicity according to the CTC Criteria (Version 4.0): All adverse events  $\geq$  Grade 3 according to CTCAE, Version 4.0 criteria, that are definitely, probably, or possibly related to the administration of the investigational agents will be assessed and described using descriptive statistics.
- Overall response rate - irOR (irBOR of irPR or irCR) according to immune-related response Criteria (ir-RC) (see 6.3.4.5), and OR (BOR of PR or CR) according to RECIST (see 6.3.3.3).
- Disease control rate - irDCR (irBOR of irCR or irPR or irSD) according to immune-related response Criteria (ir-RC) (see section 6.3.4.5), and DCR (BOR of PR or CR) according to RECIST (see 6.3.3.3).
- Progression free survival rate at 6 months. PFS is defined as the time from the first study treatment date until documented tumor progression (irPD) date (as defined by immune related response criteria) or date of death, whichever occurs first.

Exploratory endpoints

Pharmacodynamic effects of ipilimumab on Absolute Lymphocyte Count (ALC) and correlation of ALC to anti-tumor activity (ORR) of ipilimumab during induction phase (W12)

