Additional analyses treating survival and PFS as time to event endpoints will be performed i.e.: Kaplan-Meier plots will be produced. These will use the ITT population. Survival will be measured, regardless of any re-induction, from the date of the first on-study ipilimumab dose until date of death. Survival time for subjects, whose date of death is unknown, will be censored at the last date of contact. PFS will be measured, regardless of any re-induction, from the date of the first dose of ipilimumab until the first on-study documented date of progression, as per irRC, or date of death, whichever comes first. PFS time of subjects not known to progress or die, will be censored at the date of the last tumor assessment. Median survival, median PFS, survival rate at 1 year and PFS rate at 6 months, all as derived from the Kaplan-Meier curves, will be presented, together with 95%CI.

Safety will be reported for 70 days (5 half-lives) post last treatment. This period will be considered the on-study safety period. The analysis of safety will be based on the frequency of AEs and their severity for all treated subjects (i.e.: the Safety population). Worst toxicity grades per subject will be tabulated for all AEs. Additionally, drug-related grade 3 or more AEs, immune-related, and serious AEs will be tabulated separately, and listings by subject will be produced for all deaths, all SAEs and all AEs leading to discontinuation of study drug.

All adverse events and serious adverse events recorded during the study will be summarized using descriptive statistics. The incidence of treatment-emergent adverse events (new or worsening from baseline) will be summarized by body system, preferred term, verbatim of adverse event, intensity (based on CTC grades), and relation to the investigational products. Furthermore all adverse events and serious adverse events will be listed.

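### The protocol is inconsistent on when and where non-serious adverse events are collected in the 70-day safety window, so late non-serious related grade 3 or higher events may be under-ascertained

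*Protocol*

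**What the plan says.** **Analysis window.** Section 9.5 states "Safety will be reported for 70 days (5 half-lives) post last treatment". The synopsis agrees: "Safety will be reported for 70 days post last treatment. This period will be considered the on-study safety period". Section 8.3.1 collects serious adverse events over the same 70 days.

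**Collection of non-serious events.** Section 8.3.3 states "The collection of non-serious AE information should begin from time of consent forward until end of treatment" and does not define the end point. Section 6.2 sets a different one: "any occurrence of nonserious or SAE from time of consent forward, up to and including follow-up visits, will be reported".

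**The visit that closes the window.** Section 6.1.1.4 states "The end of treatment visit will be performed 10 weeks after last administration of study therapy". Its procedure list covers vital signs, physical examination, performance status, laboratory tests and "Assessment of signs and symptoms". It names neither an adverse event assessment nor concomitant medication. In the Time and Events Schedule, the adverse event row is marked for treatment and re-staging visits and is blank for the End of Treatment visit and the follow-up phase. The heading of 6.1.1.2, however, takes in the End of Treatment visit together with Visits 2 to 5. Its induction list includes both adverse event assessment and concomitant medication, and exempts only the pregnancy test from that visit.

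**Causality.** Section 8.2 begins "The following categories and definitions of causal relationship to investigational product as determined by a physician should be used" and then gives two categories, related and not related. The safety endpoint in 9.3.2 counts events of grade 3 or higher "that are definitely, probably, or possibly related to the administration of the investigational agents".

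**The concern.** Related toxicity of grade 3 or higher is the first-listed secondary endpoint. Its analysis assumes that adverse events are ascertained for 70 days after the last dose. The protocol secures this for serious events but not clearly for non-serious ones: the end date differs between sections, and the visit on the last day of the window does or does not include an adverse event assessment depending on the page consulted. Sites usually work from the schedule, which shows none.

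Patients with progression who are not eligible for re-induction have no further re-staging visits (6.1.1) and are then followed for survival only (6.1.1.5). For them the End of Treatment visit is the only remaining scheduled opportunity. If nothing is asked there, ascertainment in the later part of the window could differ between early progressors and patients who stay on re-staging.

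**Working it through.** **1. The plan's own window.** The End of Treatment visit falls at 10 weeks × 7 = 70 days, the last day of the safety period. Section 9.5 equates 70 days with five half-lives, which implies 70 × 24 / 5 = 336 h. Section 1.3.3 gives a range of 297 to 414 h, so five half-lives span 5 × 297 / 24 = 61.9 days to 5 × 414 / 24 = 86.3 days. The stated window is reproduced and is not in dispute.

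**2. Readings of the end point in 8.3.3.**
- Date of last dose: collection stops 70 days before the analysis window closes.
- The End of Treatment visit, the only visit of that name: collection matches 9.5 exactly.
- The synopsis definition of treatment, induction plus re-induction until 12 months after first dose: collection runs longer than 9.5 needs.

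Section 6.2 extends to follow-up visits, where the schedule again has no adverse event entry.

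**3. Scheduled coverage if the schedule and 6.1.1.4 are followed.** The last induction dose is on day 64 (5.1), so the window ends on day 64 + 70 = 134. Week 12 falls on about day 78 to 85.
- Days covered by the week-12 assessment: 78 − 64 = 14 to 85 − 64 = 21.
- Remaining days: 70 − 21 = 49 to 70 − 14 = 56, that is 70% to 80% of the window.

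A patient without progression is next assessed at week 24. That is after day 134, but events from the window can still be recorded then. A patient who left re-staging at week 12 has no such visit. Section 6.1.1 adds that progressors who switch to another treatment are not formally followed except for date of death, which leaves their attendance at the 10-week visit unclear.

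**4. Which events are exposed.** Table 1, all doses, N = 2901:
- Related grade 3 or 4 events: 617 + 127 = 744 patients (25.6%).
- Related serious grade 3–4 events: 469 patients (16.2%).
- Difference: 744 − 469 = 275, or 275 / 744 = 37%.

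So roughly 63% would be caught by the 70-day rule for serious events and 37% depend on non-serious collection. At 10 mg/kg the dependent share is (163 + 38 − 140) / 201 = 61 / 201 = 30%. The split is approximate because the counts are patients by worst grade.

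**5. Illustrative worst case.** Loss = R × s × w, where R is the related grade 3–4 rate, s the non-serious share and w the share with onset after last dose. The documents do not give w; 10% to 40% is assumed. Every such non-serious event is taken as lost, which overstates the loss because the week-12 visit would catch some.

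| R | s | w | Loss (percentage points) | Patients of 200 |
|---|---|---|---|---|
| 25.6% (Table 1, all doses) | 0.37 | 0.10 | 0.95 | 1.9 |
| 25.6% | 0.37 | 0.40 | 3.79 | 7.6 |
| 7% (grade 3–4 irAEs at 3 mg/kg, 1.3.4c) | 0.37 | 0.10 | 0.26 | 0.5 |
| 7% | 0.37 | 0.40 | 1.04 | 2.1 |

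If sites collect to day 70, the loss is zero.

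**6. Causality terms side by side.** Section 8.2 has two categories. Section 9.3.2 uses definitely, probably or possibly; 5.5.2 and 8.3.1 use certainly, probably or possibly; 6.3 uses at least possibly. The endpoint pools its three grades into a single yes or no, so 8.2 could supply it, but no sentence says that the related category includes possibly related.

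**The case against.** The strongest reply is that the protocol already provides what is asked. Section 6.1.1.2 covers the End of Treatment visit by its heading, and exempting the pregnancy test there makes sense only if the rest of the list applies. Read with the visit of that name, 8.3.3 matches 9.5 to the day. Section 6.2 reaches further still, 6.4.1 has adverse effects assessed continuously and all events recorded, and 8.3 makes the investigator document every event during the study. The 49 to 56 days would then be an interval between visits, and an assessment on day 134 would cover it.

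Most of this stands. It rules out saying flatly that the day-70 visit has no adverse event assessment, or that collection stops at last dose. It does not settle the matter, because the schedule and the section devoted to that visit both omit the item. The signs-and-symptoms entry does not fill the gap: the treatment and re-staging lists carry it and the adverse event assessment as separate items.

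A reader might also cite the ocular inflammation data in 1.3.5 (median onset about 61 days, range 14 to 114) as proof of loss. They do not show it. Those are serious events, which 8.3.1 collects for the full 70 days. Sections 1.3.5 and 1.4 place first endocrine onset at weeks 6 to 12 and irAEs typically during induction.

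**Conclusion.** The inconsistency is real and worth correcting. The protocol gives conflicting end points for non-serious adverse events and conflicting content for the visit that closes the safety window. If sites work from the schedule, non-serious related grade 3 or higher events late in the window may be under-ascertained, mainly in patients who progress at week 12 and leave re-staging.

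A reader might infer that the reported grade 3 or higher rate is understated. The documents do not support that: they give neither the share of events with late onset nor which section sites would follow. The illustrative range is zero to about 4 percentage points, and its upper end rests on the assumed 40% late onset, the all-dose Table 1 rates and complete loss of non-serious events after last dose. Nor do the mixed causality terms make the endpoint impossible to derive; a mapping sentence is missing.

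Serious events are covered by 8.3.1, and the primary endpoint, one-year survival, is not affected.

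**What to change.** - **8.3.3 and 6.2:** state that all adverse events are collected from consent through 70 days after the last dose, matching 8.3.1 and 9.5, and replace the undefined end point.
- **Time and Events Schedule and 6.1.1.4:** add adverse event assessment and concomitant medication to the End of Treatment visit, consistent with 6.1.1.2. Say in 6.1.1 whether progressors who switch treatment still attend it.
- **Causality, a secondary wording alignment:** reconcile 8.2 with 5.5.2, 6.3, 8.3.1 and 9.3.2, for example by stating that the related category comprises definitely, probably and possibly related. This harmonises terms only and leaves the dose-skipping and stopping rules themselves untouched.

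The cost is amendment wording and one CRF page at a visit already planned. Reported adverse event rates may be slightly higher as a result.

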#### **8.3.4. Pregnancy**

Sexually active WOCBP must use an effective method of birth control during the course of the study, in a manner such that risk of failure is minimized. Before enrolling WOCBP in this clinical study, the investigator must review the guideline about study participation for WOCBP which can be found in the GCP Manual for Investigators. The topics include the following:

- General Information
- Informed Consent Form
- Pregnancy Prevention Information Sheet
- Drug Interactions with Hormonal Contraceptives
- Contraceptives in Current Use

- Guidelines for the Follow-up of a Reported Pregnancy.

Before study enrollment, WOCBP must be advised of the importance of avoiding pregnancy during study participation and the potential risk factors for an unintentional pregnancy. The subject must sign an informed consent form documenting this discussion.

**All WOCBP MUST have a negative pregnancy test within 72 hours before receiving ipilimumab.** The minimum sensitivity of the pregnancy test must be 25 IU/L or equivalent units of HCG. If the pregnancy test is positive, the subject must not receive ipilimumab and must not be enrolled in the study.

**In addition, all WOCBP should be instructed to contact the investigator immediately if they suspect they might be pregnant (e.g., missed or late menstrual period) at any time during study participation.**

If, following initiation of the investigational product, it is subsequently discovered that a study subject is pregnant or may have been pregnant at the time of investigational product exposure, including during at least 6 half-lives after product administration, the investigational product will be permanently discontinued in an appropriate manner (eg, dose tapering if necessary for subject safety). Pregnancy occurring during the clinical investigation, although not considered a serious adverse event, must be reported to the sponsor, BMS and Alcedis GmbH within the same timelines as a serious adverse event and using the same procedure as described for the reporting of SAEs. The outcome of a pregnancy should be followed up carefully and any abnormal outcome of the mother or the child should be reported.

Any pregnancy that occurs in a female partner of a male study participant should be reported to the sponsor. Information on this pregnancy will also be reported as described for SAE-reporting.

Protocol-required procedures for study discontinuation and follow-up must be performed on the subject unless contraindicated by pregnancy (e.g., x-ray studies). Other appropriate pregnancy follow-up procedures should be considered if indicated. In addition, the investigator must report to the sponsor and BMS, and follow-up on information regarding the course of the pregnancy, including perinatal and neonatal outcome. Infants should be followed for a minimum of 8 weeks.

### **8.3.5. Other Safety Considerations**

Any significant worsening noted during interim or final physical examinations, electrocardiograms, x-rays, and any other potential safety assessments, whether or not these procedures are required by the protocol, should also be recorded in the medical record.

## **9. STATISTICAL METHODOLOGY**

In this study, up to 200 patients with unresectable stage III-IV melanoma will be treated with the anti-CTLA-4 mAb Ipilimumab monotherapy over a recruitment period of 8-9 months at up to 25 centers in Germany.

### **9.1. Sample Size Justification**

Assuming that the entire study cohort will behave as cutaneous melanoma treated with 10mg/kg including maintenance therapy, the 1-year-survival rate will be comparable to the 1-year-survival rate seen in BMS CA184-007,-008, and -022 studies, i.e about 50% (0.5), and the width of the 95% CI will maximally be 14%, corresponding to a lower confidence limit of 0.43 and an upper of 0.57. The 1-year-survival rate in the MDX010-020 study published in NEJM (Hodie et al., 2010) is 43% and the 2-year-survival rate 23% for both ipilimumab arms combined using the 3 mg/kg dosing scheme 4-times over 12 weeks.

The proposed study includes patient subgroups (uveal, mucosal) which we currently have only limited efficacy data for ipilimumab on. Retrospective studies suggest the median survival for mucosal melanoma in Stage IV is around 6 months corresponding - assuming an exponential distribution - to about 13% survival rate at 1 year, and median survival for uveal melanoma is around 11 months corresponding to about 25% survival rate at 1 year (Becker et al., 2002; Penel et al., 2008).

Given the differing median survivals for uveal and mucosal melanoma prior to treatment with ipilimumab, the OS at 1 year will be presented separately for the cohorts, uveal, mucosal and cutaneous melanoma. Assuming 10% (N=20) subjects enrolled have uveal melanoma, and a further 10% have mucosal melanoma, whilst 80% (N=160) of those enrolled have cutaneous melanoma, the width of the 95%CI will, for any survival rate at 1 year, maximally span 41% for the uveal and mucosal cohorts, and 18% for the cutaneous cohort.

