**Sample Size Justification**

Assuming that the entire study cohort of an estimated 200 patients will behave as pretreated cutaneous melanoma patients treated with 3 mg/kg and re-induction for eligible patients as in MDX010-20 trial where the median survival rate of 10.1. months and a 1-year-survival rate of 45.6 % (0.5) was seen, the width of the 95% CI will maximally be 14%, corresponding to a lower confidence limit of 0.43 and an upper of 0.57.

The study includes patient subgroups (uveal, mucosal, with or without asymptomatic brain metastases, with or without elevated LDH levels) for which we currently have only limited efficacy data for ipilimumab on. Retrospective studies suggest the median survival for mucosal melanoma in Stage IV is around 6 months (corresponding assuming an exponential distribution) to about 13% survival rate at 1 year), a median survival for uveal melanoma is around 11 months (corresponding

to about 25% survival rate at 1 year) and a median survival for asymptomatic brain metastases is around 5 months (corresponding to about 13% survival rate at 1 year) (Penel et al., Invest New Drugs, 2008; Becker et al., Brit J Cancer, 2002; [name] et al., Ann Oncol 2006).

Given the differing median survivals for uveal and mucosal melanoma prior to treatment with ipilimumab, the OS at 1 year will be presented separately for the cohorts, uveal, mucosal and cutaneous melanoma with or without asymptomatic brain metastases. Assuming 10% (N=20) subjects enrolled have uveal melanoma, and a further 10% have mucosal melanoma, whilst 80% (N=160) of those enrolled have cutaneous melanoma, the width of the 95%CI will, for any survival rate at 1 year, maximally span 41% for the uveal and mucosal cohorts, and 18% for the cutaneous cohort.

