### Statistics

The primary endpoint is the one year survival rate.

As a simple rate, it will be calculated as the number of patients being still alive 12 months after their first administration of the study treatment divided by the number of patients having received at least one administration of the study treatment. Only subjects known to be alive at 1 year will be included in the numerator. Exact (Clopper and Pearson) two-sided 95%CI will be given.

As a time to event variable, it will be derived from the Kaplan-Meier curve based on the survival data from all subjects receiving at least one administration of the study treatment. In this case missing data will be censored at the last contact. Two-sided 95%CI will be given.

Apart from the primary endpoint descriptive statistics will be used.

Results will be presented overall and per cohort (cutaneous versus uveal versus mucosal melanoma). Results may also be presented for the subgroups:

- (1) – LDH < 2 ULN versus LDH ≥ 2 ULN
- (2) - status brain mets versus no brain mets in medical history
- (3) - b-raf mutation positive versus b-raf mutation negative
- (4) - HLA-A2 positive versus HLA-A2 negative

Proportions (Survival rate at 1 year, irOR, irDCR, irPFS at 6 mths) will be presented with exact (Clopper and Pearson) two-sided 95% CI. irOR, irDCR and irPFS are defined according to the irRC. The date of origin for the survival rate at one year and irPFS at 6 months is the date of the first ipilimumab dose. Only subjects known to be progression free at 6 months / alive at 1 year will be included in the respective numerators. Any subject receiving at least one dose of ipilimumab will be included in the denominators.

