#### 9.5. Statistical analysis

The primary endpoint, one year survival rate, is based on the ITT population. As a simple rate, it will be calculated as the number of patients being still alive 12 months after their first administration of the study treatment divided by the number of patients having received at least one administration of the study treatment. Only subjects known to be alive at 1 year will be included in the numerator. As a time to event variable, it will be derived from the Kaplan-Meier curve. In this case missing data will be censored at the last contact. See below for further details.

All other analyses will have exploratory character. Results will be presented overall and per cohort/subgroup:

- (1) cutaneous vs uveal vs. mucosal melanoma
- (2) - LDH < 2 UNL versus LDH ≥ 2 UNL
- (3) - status brain mets versus no brain mets in medical history
- (4) - status Braf mutation positive versus. Braf mutation negative
- (5) - HLA-A2 positive versus HLA-A2 negative

Demographic and baseline characteristics will be tabulated for all treated subjects. For categorical variables, summary tabulations of the number and percentage within each category (with a category for missing data) of the parameter will be presented. For continuous variables, the mean, median, standard deviation, minimum and maximum values will be given.

Proportions (Survival rate at 1 year, irOR, irDCR, irPFS at 6 mths, OR and DCR) will be presented with exact (Clopper and Pearson) two-sided 95% CI. irOR, irDCR and irPFS are defined according to the irRC; OR and DCR according to RECIST; The date of origin for the survival rate at one year, and irPFS at 6 months is the date of the first ipilimumab dose. Only subjects known to be progression free at 6 months / alive at 1 year will be included in the respective numerators. Any subject receiving at least one dose of ipilimumab will be included in the denominators. The denominator for the irOS and irPFS analyses will be the ITT population. The denominator for the irOR, and irDCR, OR and DCR will be the Response-evaluable population..

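### The stated maximum CI width of 41 points for the 20-patient uveal and mucosal cohorts is wrong: the planned exact interval spans up to 46 points, and the planning text differs between the synopsis and Section 9.1

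*Protocol*

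**What the plan says.** Section 9.1 and the Sample Size Justification in the synopsis make the same cohort statement. The sizes are assumed: "Assuming 10% (N=20) subjects enrolled have uveal melanoma, and a further 10% have mucosal melanoma", "whilst 80% (N=160) of those enrolled have cutaneous melanoma". From these the protocol concludes that the 95% CI for one-year survival will, for any rate, "maximally span 41% for the uveal and mucosal cohorts, and 18% for the cutaneous cohort".

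The interval method is fixed. The Statistics section of the synopsis says of the primary endpoint as a simple rate: "Exact (Clopper and Pearson) two-sided 95%CI will be given". Section 9.5 says that proportions, one-year survival among them, "will be presented with exact (Clopper and Pearson) two-sided 95% CI".

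For all 200 patients, both places give a maximum width of 14% and limits of 0.43 and 0.57, but they reach them differently:

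- **Section 9.1** begins "Assuming that the entire study cohort will behave as cutaneous melanoma treated with 10mg/kg including maintenance therapy" and takes about 50% from three studies of that regimen.
- **Synopsis** begins "Assuming that the entire study cohort of an estimated 200 patients will behave as pretreated cutaneous melanoma patients" and refers to MDX010-20 at 3 mg/kg, where "a 1-year-survival rate of 45.6 % (0.5) was seen".

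**The concern.** N, confidence level, interval method and the claim of a maximum are all on the page, so the cohort figures can be checked without outside data. They do not come out, although the overall figure from the same paragraphs does.

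The trial has one arm and no hypothesis test, so the expected CI width is the whole case for the sample size. Section 9.1 describes the uveal and mucosal subgroups as ones with little efficacy data on ipilimumab, and one-year survival is to be shown separately for them. For these two cohorts the protocol promises more precision than the planned analysis can give. Anyone judging whether about 20 patients are informative would rely on the 41-point figure.

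The overall limits raise a lesser question: one pair of limits is printed beside two different expected rates, taken from studies of different regimens.

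**Working it through.** **Inputs.** N=20 (uveal), N=20 (mucosal), N=160 (cutaneous) and N=200 (all), from Section 9.1 and the synopsis. Two-sided 95% Clopper-Pearson interval, from Section 9.5 and the synopsis.

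**Formula.** For x survivors out of n, the lower limit is the 0.025 quantile of Beta(x, n−x+1) and the upper limit is the 0.975 quantile of Beta(x+1, n−x). The maximum width is the largest difference over x = 0, …, n.

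**Step 1: the overall figure reproduces.** At n=200, x=100 the limits are 0.4287 and 0.5713, a width of 14.3 points. This agrees with the stated 14% and 0.43 to 0.57. The normal approximation, 2 × 1.96 × √(0.25/200), gives 13.9 points.

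**Step 2: the cohort maxima do not.**

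| n | x at maximum | Exact limits | Exact width | Stated |
|---|---|---|---|---|
| 20 | 10 | 27.2% to 72.8% | 45.6 points | 41 |
| 160 | 80 | 42.0% to 58.0% | 16.0 points | 18 |

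At n=20 the stated figure is 45.6 − 41 = 4.6 points too small. At n=160 it is 18 − 16.0 = 2.0 points too large.

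**Step 3: where the 41-point bound fails at n=20.**

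| x/20 | 3 | 5 | 6 | 7 | 8 | 9 | 10 |
|---|---|---|---|---|---|---|---|
| Exact width (points) | 34.7 | 40.4 | 42.4 | 43.8 | 44.8 | 45.4 | 45.6 |

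The widths are symmetric about 10/20, so the bound is exceeded from 6/20 to 14/20, that is, for observed survival from 30% to 70%.

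**Step 4: would another method explain the figures?** Full widths at p=0.5, in points:

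| Method | n=20 | n=160 |
|---|---|---|
| Normal approximation | 43.8 | 15.5 |
| Normal approximation, continuity-corrected | 48.8 | 16.1 |
| Wilson | 40.1 | 15.3 |
| Wilson, continuity-corrected | 44.3 | 15.9 |
| Jeffreys | 41.3 | 15.4 |
| Mid-P | 42.3 | 15.4 |

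Only Jeffreys gives 41 at n=20, none gives 18 at n=160, and none gives both. With the exact method, maxima of 41 and 18 points correspond to about 25 and 127 patients.

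**Step 5: the synopsis limits.** 45.6% of 200 is 91.2, so x=91. The exact limits are 0.385 and 0.527, a width of 14.2 points. The printed lower limit of 0.43 is 4.5 points above 0.385, but the width is practically the same as at 50%.

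**The case against.** Several points on the other side are sound.

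- **The 18% is not violated.** A reader might put both cohort figures down as equal errors. The text gives an upper bound, and 16.0 lies below 18, so the statement is true and cautious. Only the 41% is broken.
- **The limits 0.43 to 0.57 are right in Section 9.1**, which assumes about 50%. The mismatch is confined to the synopsis, which itself puts 0.5 in brackets after 45.6% and so uses the widest case. The shift of 4.5 points moves the centre of the interval and loses no precision, and no decision depends on 0.43.
- **There are not three rival planning rates.** A reader might add the 43% in Section 9.1 to the 45.6% and the 50%. That section gives 43% for both ipilimumab arms of MDX010-20 combined and does not plan with it. The two planning bases lead to the same N, width and limits.
- **The trial was not opened for the uveal and mucosal cohorts alone.** Its primary endpoint concerns the complete population and its rationale is a broad pretreated one. Section 9.5 calls all other analyses exploratory, and N=20 is an assumed share rather than a recruitment target.
- **At low survival the bound holds.** At the historical rates that the protocol states, 13% (mucosal) and 25% (uveal), the widths are about 34.7 points (3/20) and 40.4 points (5/20).

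The last point softens the error but does not remove it. The claim is made for any survival rate, and survival on treatment may be higher than those rates. The uveal median of 11 months, under the exponential assumption that the protocol names, gives 0.5^(12/11) = 47% at one year, where the width is about 45 points.

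**Conclusion.** The concern holds for the 20-patient cohorts. The stated maximum of 41 points should be 45.6, so it is 4.6 points too small (4.6/41 = 11% of the stated figure), and it fails for every result from 6/20 to 14/20. The 160-patient figure is looser than it need be, by 2.0 points, and misleads nobody to the trial's advantage. The 14-point overall width stands.

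The synopsis prints limits for 50% beside 45.6%, and the two sections cite different source studies. Both are inconsistencies of presentation with no effect on N or on the overall width.

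This rests on the cohort sizes that the protocol assumes and on the exact method that it prescribes; realised widths will depend on how many patients of each type enter. No type I error or power is involved, because nothing is tested. The correction should be made because CI width is the only sample-size argument, but it does not put the primary analysis in doubt.

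**What to change.** In both Section 9.1 and the synopsis, restate the maximum exact 95% CI widths as 46 points for N=20, 16 points for N=160 and 14.3 points for N=200, and name the Clopper-Pearson method beside them.

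Reconcile the two places to one planning basis and one expected one-year rate, and print the limits that belong to it: 0.43 to 0.57 for 50%, or about 0.385 to 0.527 for 45.6%.

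This is a change of text only and leaves the sample size as it is. The cost is that the stated precision for the uveal and mucosal cohorts becomes less favourable; for the cutaneous cohort it improves slightly.
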